## Abstract

**Background:**

Adolescents with type 1 diabetes face demanding challenges due to conflicting priorities between psychosocial needs and diabetes management. This conflict often results in poor glycaemic control and discord between adolescents and parents. Adolescent-parent conflicts are thus a barrier for health care providers (HCPs) to overcome in their attempts to involve both adolescents and parents in improvement of glycaemic control. Evidence-based interventions that involve all three parties (i.e., adolescents, parents and HCPs) and are integrated into routine outpatient clinic visits are lacking. The Guided Self-Determination method is proven effective in adult care and has been adapted to adolescents and parents (Guided Self-Determination-Young (GSD-Y)) for use in paediatric diabetes outpatient clinics. Our objective is to test whether GSD-Y used in routine paediatric outpatient clinic visits will reduce haemoglobin A1c (HbA1c) concentrations and improve adolescents' life skills compared with a control group.

**Methods/Design:**

Using a mixed methods design comprising a randomised controlled trial and a nested qualitative evaluation, we will recruit 68 adolescents age 13 - 18 years with type 1 diabetes (HbA1c > 8.0%) and their parents from 2 Danish hospitals and randomise into GSD-Y or control groups. During an 8-12 month period, the GSD-Y group will complete 8 outpatient GSD-Y visits, and the control group will completes an equal number of standard visits. The primary outcome is HbA1c. Secondary outcomes include the following: number of self-monitored blood glucose values and levels of autonomous motivation, involvement and autonomy support from parents, autonomy support from HCPs, perceived competence in managing diabetes, well-being, and diabetes-related problems. Primary and secondary outcomes will be evaluated within and between groups by comparing data from baseline, after completion of the visits, and again after a 6-month follow-up. To illustrate how GSD-Y influences glycaemic control and the development of life skills, 10-12 GSD-Y visits will be recorded during the intervention and analysed qualitatively together with individual interviews carried out after follow-up.

**Discussion:**

This study will provide evidence of the effectiveness of using a GSD-Y intervention with three parties on HbA1c and life skills and the feasibility of integrating the intervention into routine outpatient clinic visits.

Danish Data Association ref nr. 2008-41-2322

**Trial registration:**

ISRCTN54243636

## Background

Type 1 diabetes in adolescents is a challenge for the teenagers, their parents and the diabetes health care providers (HCPs) [1]. Despite new medical treatment modalities, the prognosis for childhood-onset type 1 diabetes remains poor [2,3]. The number of life years lost remains unchanged over the last four decades at approximately 17 years for a child diagnosed with type 1 diabetes at the age of 10 years [4]. Keeping blood glucose levels as close to normal as possible from as early in the disease as possible is known to prevent or postpone late diabetic complications [5-8]. The recommended target for haemoglobin A1c (HbA1c) in adolescents with type 1 diabetes is less than 7.5% without increasing the occurrence of hypoglycaemia [9]. However, adolescents typically do not maintain the necessary degree of diabetes self-management or the recommended HbA1c levels [10,11]. In Denmark, 31% of affected adolescents meet the recommended HbA1c threshold [12]. Although late diabetic complications are rarely seen during adolescence, there is evidence that their pathogenesis begins soon after diagnosis and accelerates during puberty [13,14].

### Challenges faced by adolescents trying to integrate diabetes into their lives

Most adolescents experience difficulties integrating the diabetes regimen into their lives; they confront significant conflicts between the need for diabetes management and psychosocial developmental needs and challenges [1,15]. Belonging to a peer group and fitting into the group's social norms and behaviours may be perceived as more important to the quality of a teenager's life than diabetes treatment [16]. Avoiding taking care of the disease as advised by HCPs and parents often leaves the adolescents with feelings of guilt, a conflicted conscience and frustration [17]. At the same time, they have conflicting experiences of being watched over, blamed and controlled by their parents [18], while also being vulnerable to the disease [19] and still needing guidance from their parents to manage the daily treatment [20-22]. This increases conflicts and deteriorates adolescent-parent collaboration and adolescent self-management [23,24]. From the adolescent's point of view, striving for independence and self-management of the disease is known to present a considerable stress [25,26].

### Challenges faced by parents in transferring responsibility

During adolescence, the responsibility for the management of diabetes should gradually be transferred from parents to adolescents [1,27]. Some parents are, however, reluctant to transfer responsibility for diabetes management, as they doubt the adolescents' abilities to self-manage their diabetes [28,29]. Other parents leave all responsibility for managing the disease to their adolescents, trying to avoid conflicts or expecting them to be competent because of their age and the amount of time since diagnosis [30]. Both approaches may lead to poor glycaemic control [31,32]. A constructive form of parental involvement comprising guidance and supervision, shared knowledge and shared responsibility yields better glycaemic control [33]. However, systematic education and guidance on how to be a constructive and supportive parent is not currently offered as part of routine care [34,35].

### Challenges faced by health care providers in their interactions with adolescents and parents

HCPs view adolescence as a difficult time in which the processes of managing diabetes, providing guidance and eliciting cooperation from adolescents and their parents are complex [36-38]. Apart from optimising medical treatment for diabetes, HCPs should aim to effectively navigate the interaction between adolescents struggling to find their identity separate from their parents and parents concerned about their child's difficulties combining teenage life with diabetes self-management [39]. HCPs should encourage parental involvement that facilitates adolescents' independent decision-making through a gradual transfer of responsibility and management of the disease [40-42]. However, current diabetes education and routine outpatient clinic visits seem to have little effect on conflict resolution, transfer of responsibility, self-management skills, and better glycaemic control [43].

### Interventions

According to Anderson [24] and Delamater [44], psychosocial and behavioural family-based controlled interventions improve self-management, glycaemic control and family relationships. However, these interventions were carried out separate from routine paediatric outpatient clinic visits. Three randomised controlled studies have partly been integrated into routine paediatric outpatient clinics [43,45,46], and two of these studies included parents (Laffel [46] and Murphy [43]). Grey and colleagues have shown that coping skills training delivered to small groups of adolescents combined with intensive diabetes management improved quality of life and glycaemic control [45]. Laffel and colleagues have shown that a family-focused teamwork intervention run by a trained research assistant increased family involvement and prevented worsening of glycaemic control [46]. Murphy and colleagues have shown potential benefits on parental involvement and glycaemic control in a structured education programme for adolescents and parents in small groups, but further studies are in progress to confirm these findings [43].

In searching for a method that could be applied by HCPs and adapted to adolescents and their parents, we chose Guided Self-Determination (GSD), which has reduced HbA1c (by 0.4%) and improved life skills in adults with persistently poor glycaemic control of type 1 diabetes [47]. We adjusted GSD to adolescents and their parents (GSD-Young, named GSD-Y hereafter) for use in paediatric diabetes outpatient clinics by the adolescents' usual HCPs. The current trial of GSD-Y is the first to evaluate the effect of an intervention involving both adolescents and parents that is carried out in routine outpatient clinics with HCPs from the adolescents' usual interdisciplinary diabetes team.

We hypothesize that using GSD-Y in routine paediatric outpatient diabetes clinics will reduce HbA1c concentrations and improve adolescents' life skills compared with those in a control group.

### Objectives

1) To test whether GSD-Y can be integrated into routine paediatric outpatient diabetes clinics in a collaboration between adolescents, their parents and the interdisciplinary diabetes HCPs.

2) To test whether GSD-Y reduces HbA1c and improves life skills in adolescents with type 1 diabetes.

3) To illustrate how GSD-Y influences developing life skills in adolescents supported by their parents and their HCPs.

## Methods/Design

### Ethical Approval

The trial will be performed in accordance with the recommendations guiding nurses in clinical research involving human participants (Helsinki Declaration). The project was reviewed by the Danish National Committee on Biomedical Research Ethics on April 17, 2009 as registry- and interview-based research (REC; reference number, 0903054 document number, 230436).

### Type of study

This study is a life-skills intervention using a mixed methods design comprised of a randomised controlled trial and a nested qualitative evaluation [48]. Objective 2 will be met through the quantitative component, whereas Objectives 1 and 3 will be met through the qualitative component. The use of a quantitative and a qualitative approach in combination increases the opportunity for a complementary evaluation, which provides a better understanding of GSD-Y's potential to influence the process of improving glycaemic control and life skills than using either approach alone. The quantitative component evaluates the effect of GSD-Y, whereas the qualitative component has two purposes: a) to elucidate the factors that affect how well GSD-Y is implemented in routine clinics and perhaps affects the outcomes, and b) to provide a detailed understanding of how GSD-Y works in triads carried out as part of routine care delivered by the adolescents' usual HCPs.

The protocol is summarised in a flowchart (Figure 1).

**Figure 1 F1:**
[figure not shown]
Flowchart of the study

### Setting

The study takes place at 2 paediatric outpatient clinics at 2 hospitals in the capital region of Denmark: Glostrup, with the largest diabetes outpatient clinic in Denmark (480 patients) and Hillerød, with the third largest diabetes outpatient clinic in Denmark (171 patients).

Two paediatric physicians, 5 paediatric diabetes nurses and 2 dieticians (HCP hereafter), trained and tested in using GSD-Y, will recruit adolescents with type 1 diabetes and conduct the GSD-Y intervention as part of their routine outpatient clinic visits.

### Guided Self-Determination-Young: theoretical and conceptual frameworks

GSD is a problem-solving and decision-making method designed to overcome barriers to empowerment in adult patient-provider interactions, and these barriers are explained by three grounded theories [49-51]. GSD has a formal theoretical foundation in life-skills theory [52,53], empowerment [54] and motivational theory of self-determination [55,56].

GSD-Y is aimed at improving glycaemic control and increasing adolescents' life skills. Life skills is defined as "those personal, social, cognitive and physical skills that enable people to control and direct their lives and develop the capacity to live with and produce change in their environment" [47,52,57]. In GSD-Y, the acquisition of life skills is considered to be a developmental process, where the adolescents are intended to start to accept and integrate diabetes into their lives and to become autonomously motivated to handle the challenges the life of a teenager with type 1 diabetes demands. To be autonomously motivated means, for example, that adolescents check their blood sugar because they find it important personally, rather than doing it on the initiative of parents or HCPs [56].

Because part of developing life skills is making self-determined decisions [52], Self-Determination Theory (SDT) has a central role in GSD-Y. According to SDT, self-determined behaviour requires the fulfilment of three needs: competence, autonomy and relatedness. An environment that is autonomy-supportive is necessary to foster the fulfilment of these needs [56]. A feeling of competence occurs when a person perceives that he or she meets optimal challenges and is able to master them effectively. Autonomy is perceived when people experience a sense of choice, endorsement and volition to act in accordance with their interests and values. The need for relatedness refers to the warmth and caring received through interactions with others, resulting in a general sense of belonging [56]. However, by applying pressure in their striving for good glycaemic control, parents and HCPs may unwillingly obstruct the adolescents' development of competence, autonomy and relatedness, potentially fostering passivity, ill-being and amotivation [58].

In our study, the adolescents' need for relatedness is satisfied when they feel a sense of belonging with parents and HCPs because there is an atmosphere where talking openly and honestly about their difficulties living with diabetes is legitimised, and adolescents still feel that they are cared for unconditionally. Satisfaction of the need for autonomy occurs when the adolescents perceive that parents and HCPs try to understand their perspective, acknowledge their feelings, and act in a non-judgmental way by minimizing the use of controlling language and behaviour. This creates an autonomy-supportive environment for decision-making, which helps adolescents act in congruence with their values and interests. Satisfying the need for relatedness and autonomy paves the way for fulfilling the need for competence in diabetes management. Adolescents will believe that they succeed in managing diabetes because parents and HCPs are aware of their current competence and accept their shifting readiness to take responsibility for their diabetes.

### Guided Self-Determination-Young: essentials in GSD-Y

GSD-Y consists of 18 semi-structured reflection sheets for adolescents (Table 1) and 5 reflection sheets for parents (Table 2). In addition, 4 new semi-structured reflection sheets have been developed for visits with dieticians (Table 3). The semi-structured reflection sheets are based on theories such as dynamic judgement building [59], values clarification [60] and the trans-theoretical stages of change theory [61], all of which enhance the development of life skills as described above.

**Table 1 T1:** Reflection sheets for adolescents

1. visit	Your life with diabetes from beginning to now
**Reflection sheets**	Written invitation to work together in a new way
	Two ways to look at HbA1c Important events and periods in your life What do you find difficult at present living with your diabetes? Your plans for changing your way of life Agreement on things to work with till next visit

**2. visit**	**Values and opportunities**

**Reflection sheets**	Unfinished sentences: needs, values, experiences and opportunities?
	Agreement on things to work with till next visit

**3. visit**	**Diabetes in your life - now and in the future**

**Reflection sheets**	Blood sugar checks and your reasons for checking
	A picture or a metaphor, or expression describing your life with diabetes Room for your diabetes in your life Shared responsibility for your diabetes in daily life between you and your parents Agreement on things to work with till next visit

**4. visit**	**Different ways to look upon numbers**

**Reflection sheets**	Your blood-sugar numbers as you would wish them to be and as you know them from experience
	Evidence for advantages and disadvantages of high and low blood sugar Your plan for blood sugar regulation in the short and long run Situations where you want to avoid low blood sugar Agreement on things to work with till next visit

**5. visit**	**Problem-identification**

**Reflection sheets**	Current problem-solving
	Agreement on things to work with till next visit

**6. visit**	**Problem solving and options of new ways to self-management**

**Reflection sheets**	Dynamic problem-solving
	Pros and cons Agreement on things to work with till next visit

**7. visit**	**Problem-identification**

**Reflection sheets**	Current problem-solving
	Agreement on things to work with till next visit

**8. visit**	**Problem solving and options of new ways to self-management**

**Reflection sheets**	Dynamic problem-solving
	Pros and cons Solved problems and subjects to continue to work with in future outpatients appointments

**Table 2 T2:** Reflection sheets for parents

1. visit	Your life as a parent to an adolescent with type 1 diabetes
**Reflection sheets**	Unfinished sentences: needs, values, experiences and opportunities?
	Room for your adolescents' diabetes in your life Current problem-solving

**2. visit**	**Problem identification and solving - options of new ways to shared decision making**

**Reflection sheets**	Dynamic problem-solving
	Pros and cons

**Table 3 T3:** Reflection sheets for visits at the dietician

1. visit	Present challenges regarding food, snacks and insulin
**Reflection sheets**	What do you find demanding or difficult at present regarding your food living with your diabetes?
	Experiments: An easy situation and a difficult situation as you experience it where you try to get food/snacks and insulin to fit together

**2. visit**	**Evaluation of experiments**

**Reflection sheets**	Did it work? Why if and why if not?
	New experiments to work with till next visit or ending

Before each appointment, adolescents and parents complete the reflection sheets (Table 1, 2, 3). The first reflection sheet includes a written invitation for adolescents and their parents to take part in mutual problem solving (Table 1) [50]. While this component of the sheet clarifies that the knowledge of all three parties is important and legitimises different points of view, it also states that the adolescents are seen as the final problem solvers, and parents and HCPs are seen as facilitators.

By filling in reflection sheets with their own words and drawings, adolescents and their parents systematically explore and express their individual and common difficulties and experiences with diabetes in daily life. Thus prepared for appointments in the outpatient clinics, adolescents and their parents are guided by trained GSD-Y HCPs to communicate openly and reflect mutually by sharing and respecting each other's observations, thoughts and feelings as a starting point for a constructive collaboration in a caring relationship. This model adds shared insight to previous patterns of diabetes management, which yields a platform for identifying unknown resources in both adolescents and parents and discovering new strategies for problem-solving between the three parties. This paves the way for agreements and concrete arrangements about how to test new problem-solving strategies in the time between outpatient appointments. At the outpatient appointments, the triad evaluates their experiences with these strategies.

The overall aim is for adolescents and parents to identify concrete potential for change [47] and to avoid adolescents, parents or HCPs entering alliances with one another against the third party.

To use the reflection sheets with adolescents and parents, HCPs must be able to practice advanced communication skills such as mirroring [62], active listening [63,64] and values clarification [60]. Furthermore, HCPs should be able to support autonomy in their way of providing information and research-based knowledge of diabetes treatment and management (e.g., evidence on risks incurred by high and low blood sugar levels).

### Endpoints of the study

#### Primary outcome

HbA1c.

#### Secondary outcomes

a. Development of life skills in adolescents with type 1 diabetes

(i) Experience of feeling competent in managing diabetes, (ii) experience of HCPs being autonomy-supportive versus controlling, (iii) motivation for diabetes management, (iv) ability to manage diabetes-related distress, (v) involvement and support for autonomy from parents, (vi) well-being.

b. Diabetes outcomes directly related to patient management

(i) Insulin delivery/number of injections/insulin types, (ii) number of self-monitored blood glucose values, (iii) hypoglycaemic episodes (frequency and severity), (iv) admissions to hospital and reasons for admissions (e.g. episodes of ketoacidosis, hypoglycaemia).

c. Diabetes outcomes indirectly related to patient management

(i) Attendance at intervention or control sessions, (ii) parental participation.

### Sample size calculation

The size of the study was based on the primary outcome measure HbA1c. According to a power calculation, an absolute difference of 1.0% in HbA1c between the GSD-Y group and the control group (power 0.8; two-sided level of significance 0.05) could be detected with 26 patients in each group. This calculation was based on a standard deviation of the HbA1c value of 1.3% from a study of coping skills training [45]. To compensate for an attrition rate of 25%, we aimed to recruit 68 patients.

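### Minor: as printed, 26 per group and 68 recruited fall slightly short of the stated 80% power; after 25% attrition the inputs give about 77% to 78%

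*Protocol article*

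**What the plan says.** All the inputs stand in one paragraph, the Sample size calculation section of the protocol article. The target is "an absolute difference of 1.0% in HbA1c between the GSD-Y group and the control group", and of this the section says: "power 0.8; two-sided level of significance 0.05) could be detected with 26 patients in each group". That is 52 evaluable in total. The variability is sourced as follows: "This calculation was based on a standard deviation of the HbA1c value of 1.3% from a study of coping skills training". The recruitment target follows: "To compensate for an attrition rate of 25%, we aimed to recruit 68 patients". The Randomisation section splits the 68 into 34 and 34.

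The article does not name the formula, the test or the software behind the calculation. Nor does it show the step from 26 per group to 68. The Analysis section says only that suitable parametric or non-parametric tests will be used, depending on normality.

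**The concern.** The section gives a complete set of inputs and two results, so both results can be checked without any outside source. Neither comes out exactly. The sample size for 80% power is a minimum and so is rounded up, yet the printed 26 lies just below the computed value. The recruitment target, reduced by the plan's own attrition rate, does not return the plan's own evaluable number.

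This power statement is the only one given for the primary comparison. A reader of the final report, particularly of a null result, will take 80% for a 1.0% difference as the design's sensitivity. The figure should be one that the inputs support.

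**Working it through.** **Inputs** (all from the Sample size calculation section, except the 1:1 split, which is in Randomisation): difference d = 1.0; SD s = 1.3; two-sided alpha 0.05 (z = 1.960); power 0.80 (z = 0.842); attrition 25%; recruited 68, as 34 + 34.

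**Step 1: the plan's 26 per group.** The normal formula is n = 2 × (1.960 + 0.842)² × s² / d². With unrounded z-values, n = 2 × 7.849 × 1.69 / 1.0 = 26.53, which rounds up to 27. The stated 26 is therefore reproduced to within one patient per group. A one-sided test would need 21, so it does not explain 26.

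**Step 2: power around 26 per group.** The normal approximation is Φ(d / (s × √(2/n)) − 1.960). At n = 26 this is Φ(2.774 − 1.960) = Φ(0.814) = 0.792. The t-test values come from the noncentral t distribution with 2n − 2 degrees of freedom.

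| Per group | Normal | t-test |
|---|---|---|
| 26 | 79.2% | 77.6% |
| 27 | 80.7% | 79.2% |
| 28 | 82.1% | 80.7% |

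The first n to reach 80% is 27 by the normal formula and 28 by the t-test.

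**Step 3: attrition.** 68 × 0.75 = 51, one below 2 × 26 = 52. To retain 52 after 25% loss, recruit 52/0.75 = 69.3, so 70. Put the other way, 68 recruited retains 52 if attrition is 1 − 52/68 = 23.5%.

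**Step 4: power at 51 evaluable (25 + 26).** For the normal approximation, d / (s × √(1/25 + 1/26)) = 1 / (1.3 × 0.2801) = 2.746, and Φ(2.746 − 1.960) = 78.4%. The t-test gives 76.8%. The shortfall from 80% is 1.6 points (normal) or 3.2 points (t-test).

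**Step 5: difference detectable with 80% power at 51 evaluable.** Normal: (1.960 + 0.842) × 1.3 × 0.2801 = 1.02. t-test: about 1.04, where power is 79.95%.

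**For scale.** With no attrition, 34 per group gives 88.7% (normal) or 87.8% (t-test). Reaching 80% strictly after 25% attrition would take 54/0.75 = 72 recruited (normal), or 28/0.75 = 37.3, so 38 per arm and 76 in all (t-test).

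**The case against.** The strongest reply is that the plan's figure does reproduce. Power of 79.2% prints as 0.8, and the gap is half a patient per group. The larger shortfall appears only with the t-test, which the article does not name for this calculation.

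The SD is also printed to one decimal and comes from a cited study that is not at hand. Values that print as 1.3 include 1.25 and 1.26, for which the t-test needs exactly 26, and 1.28, for which the normal formula gives 25.7 and so 26. The opposite is equally possible: an SD of 1.34 would need 29 (normal) or 30 (t-test).

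Finally, the consequence is small. The one missing completer costs 0.8 points (77.6% to 76.8% by the t-test), and uncertainty in the SD or the attrition rate moves power by more than that.

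Most of this stands, and it is why the point is minor. It does not remove the point. With the printed inputs, neither method reaches 80% at 26 per group, and the attrition step depends on neither the test nor the SD: 68 less a quarter is 51.

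A reader might go further and infer that both figures were rounded in the favourable direction. The documents do not show that. The 26 may come from an unrounded SD, and the 68 could come from 27 × 1.25 = 33.75, rounded up to 34 per arm. That route does not match the printed 26 and still leaves 51 evaluable, but it means that the direction of rounding cannot be asserted.

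**Conclusion.** The point holds as a minor inaccuracy. As printed, 26 per group is one patient short by the normal formula and two by the t-test, and 68 recruited leaves one evaluable patient fewer than the plan's own 52. Power after the planned attrition is about 77% (t-test) to 78% (normal), not 80%.

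This rests on the SD being 1.3% as printed, attrition of exactly 25%, and an unadjusted comparison of two means at two-sided 0.05. Which end of the range applies depends on a method that the article does not state.

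A reader might infer that the trial is materially underpowered or should recruit more. The figures do not support that: the gap is 1.6 to 3.2 points, equivalent to a detectable difference of 1.02% to 1.04% instead of 1.0%, and better retention than planned would more than close it. Nor can a gain from baseline adjustment be credited, because the article specifies neither such an analysis nor a correlation from which to compute it.

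**What to change.** Keep 68 and replace the power statement in the Sample size calculation section with wording such as:

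> With 68 recruited and about 51 evaluable after 25% attrition, the trial has about 77% power (two-sample t-test) to 78% power (normal approximation) at two-sided 0.05 for a 1.0% difference in HbA1c with an SD of 1.3%. This corresponds to 80% power for a difference of about 1.04% (t-test) or 1.02% (normal approximation).

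Name the method used and keep only the figure that belongs to it. If the cited study gives the SD to more decimals, print that value and recompute from it.

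The cost is one sentence and a slightly less favourable stated power. Recruitment, allocation and analysis do not change.
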